## Introduction

### Background and rational

Navigational surgery including mapping and tailoring of resection margins can be a solution to the major problem of colon cancer surgery: finding “the least possible not to compromise oncological safety” resection clearance for each patient. Mentioned concept has already been discussed^[1,2]^. But although the idea that all patients are different and therefore require different approaches sounds reasonable, this notion has not met sufficient response because yet there is no tool with proven effectiveness to implement it.

However, there is a lot of evidence on ICG fluorescent imaging for visualization of locoregional lymphatic paths of colonic lesions^[2,3]^, which can guide tailoring. ICG was firstly implemented as a sentinel lymph node detection (SLND) tool but was found to lack accuracy and standardization. Ankersmit *et al* analyzed 8 studies describing 227 SLN procedures in a meta-analysis in 2019 and observed low pooled sensitivity of 63%, negative predictive value 81% and detection rate of 94%^[4]^. The same year Villegas-Tovar *et al* reported similar findings in another meta-analysis of ICG SLND accuracy for colon cancer: they calculated detection rate of 91% (80–98%), sensitivity of 64.3% (51–76%), and specificity of 65% (36–85%) – and concluded that overall ICG performance for detection of lymph node metastases is poor^[5]^. So, it was shown that ICG does help to visualize lymphatics, but it does not work for SLND in colon cancer.

Moreover, assessment of fluorescence and fluorescent lymph node harvest are affected by multiple factors. In particular, 2023 systematic review and meta-analysis of 58 prospective designed studies by Lucas *et al* showed that injection time had a significant impact on aberrant drainage detection favoring preoperative tracer injection^[6]^. The same year Kinoshita *et al* in their series of 56 cases observed both cases with metastatic lymph nodes only in the area along the ICG-stained vascular pedicles and lymph node metastasis in areas along the ICG-unstained vascular pedicles^[7]^.

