### Trial design

#### Design

This is an interventional phase II trial with single group assignment investigating feasibility of defining colon resection margins for colon cancer with ICG by comparing lymphatic distribution of subserosally injected dye with actual spread of lymphatic metastases reported by pathologists after specimen examination.

This is a single center trial. To ensure adherence to the protocol and to avoid logistical and monitoring issues stemming from multicenter design, all patients are enrolled in one center. The study includes ICG lymphatic mapping procedure and extensive pathological evaluation of the specimen, which are not routinely performed in majority of centers. Also, the calculated sample size of 101 is a number of patients, which is possible to enroll in a single center during reasonable time period. So, the risks of type II error, methodological error leading to bias and contradicting results issue, resulting from single center approach were acknowledged and study protocol created to possibly minimize them and ensure that the statistical hypothesis is tested.

Since the main focus of the study is investigation of ICG lymphatic mapping feasibility and currently there is no gold standard of lymphatic mapping for colon, no control group was included.

After signing an informed consent and undergoing screening procedure eligible patients are assigned for colonic resection with ICG lymphatic mapping. The fluorescence is assessed before specimen removal (Fig. 2) and its mesenteric distribution is marked by surgeon on the specimen (Fig. 3). During pathological examination each lymph node is assessed both for presence of metastases and for its exact location in relation to margins of ICG distribution (each lymphatic node is classified according to Japanese classification of lymphatic node groups^[15]^; D1 nodes are also classified according to their distance from primary tumor^[16]^). All screening, intraoperative, postoperative, and pathological data is recorded for further analysis. Protocol synopsis is presented in Table 2.

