### Sample size calculation and statistical analysis

As the study is aimed to access if ICG mapping can be used to reliably define resection margins in colon cancer surgery, a case of affected lymph nodes only within fluorescence margins was regarded as a true positive case, no fluorescence in pN0 – true negative, pN+ because of metastatic lymph nodes outside fluorescence zone – false negative, pN0 despite presence of fluorescence – false positive.

Sample size of 101 patients was calculated using Buderer method^[19]^ with a confidence level (1 – *α*) of 0.95 as a minimum of cases required to test accuracy of lCG lymphatic mapping for estimated sensitivity of 0.99 and precision (margin of error) of 0.03. This resulted in sensitivity threshold of 0.96. The calculation was performed for minimum acceptable kappa (k0) of 0.6, expected kappa (k1) 0.9. The resultant estimated power (1 – *β*) is 0.96. The average of pN+ cases in our center (42%) was used as prevalence – proportion of outcome (p).

For statistical analysis of primary endpoint, sensitivity will be calculated according to standard formula (number of true positive cases divided by sum of true positive and false negative cases) and its meaning will be compared to the estimated 0.99 ± 0.03. For analytical purposes other measures of accuracy will be calculated as well.

“Intent-to-treat” analysis will be performed, thus once enrolled patients are to be analyzed, irrespective of received treatment. To focus on specificities ICG spread regardless of influence of patients with treatment deviations and those with unsuccessful ICG injection, “per-protocol” analysis will be performed as well.

For secondary endpoints type of analysis will depend on nature of the data. Descriptive statistics will be used to depict feasibility of ICG lymphatic mapping, incidence of adverse events, incidence of lymph node metastases outside conventional resection margins and proportion of operations which extent is affected by ICG lymphatic mapping. Lymph node metastases pattern will be assessed as calculation of frequency of affected nodes related to number of studied nodes in each group. Parametric and non-parametric criteria will be used to compare mean values and contingency tables.

In cases of missing data, should more than 10% of data be missing, the variable will be deleted, because estimates are likely to be biased^[20]^. In other situations multiple imputations will be used.

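### The stated power of 0.96 is that of a kappa test on all 101 patients, not of the sensitivity endpoint, which rests on about 42 pN+ patients and was sized for precision

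*Protocol article*

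**What the plan says.** All of this stands in the protocol article, mainly under Sample size calculation and statistical analysis.

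- Method: "Sample size of 101 patients was calculated using Buderer method", with "a confidence level (1 – *α*) of 0.95", "estimated sensitivity of 0.99 and precision (margin of error) of 0.03", and the centre's 42% pN+ rate as prevalence. "This resulted in sensitivity threshold of 0.96".
- Kappa and power: "The calculation was performed for minimum acceptable kappa (k0) of 0.6, expected kappa (k1) 0.9". The next sentence gives the resulting estimated power as 0.96.
- Primary analysis: "sensitivity will be calculated according to standard formula (number of true positive cases divided by sum of true positive and false negative cases"). The result is compared with 0.99 ± 0.03. Other accuracy measures are promised but not named.
- Endpoint: the Endpoints section restricts the denominator to pN+ patients.
- Decision rule: the synopsis (Table 2) treats an observed sensitivity of 96% or higher after 101 procedures as success. The Abstract says more than 96%.

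**The concern.** Two unrelated calculations share one paragraph. The first fixes the half-width of a confidence interval for sensitivity; it has no null hypothesis, so no power can result from it. The second contrasts two kappa values, and kappa appears nowhere else in the document. The power is nevertheless presented as a result of the sizing for the sensitivity endpoint, beside a sensitivity threshold that happens also to be 0.96.

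A reader would take it that the trial has a 96% chance of reaching the right conclusion about sensitivity, with the error control that the word power implies. Per the Abstract, meeting the rule is meant to support tailoring resection margins to ICG spread, so the stated reliability of that rule should be its own.

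**Working it through.** **Inputs (Sample size section).** Expected sensitivity 0.99; margin 0.03; confidence 0.95; prevalence 0.42; k0 = 0.6; k1 = 0.9; N = 101. Sidedness is not stated; two-sided 5% is used here.

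**1. The sample size reproduces.**
pN+ patients needed = 1.96² × 0.99 × 0.01 / 0.03² = 42.26.
Total = 42.26 / 0.42 = 100.6, so 101.
This is a correct precision calculation, and the endpoint rests on about 42 pN+ patients.

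**2. The printed power reproduces as a kappa power.** Use the goodness-of-fit test for kappa with a binary outcome and π = 0.42. The cell probabilities are π² + π(1−π)k (both positive), 2π(1−π)(1−k) (discordant) and (1−π)² + π(1−π)k (both negative).

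| Cell | k = 0.6 | k = 0.9 | Difference² / value at k = 0.6 |
|---|---|---|---|
| Both positive | 0.3226 | 0.3956 | 0.0166 |
| Discordant | 0.1949 | 0.0487 | 0.1096 |
| Both negative | 0.4826 | 0.5556 | 0.0111 |

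The last column sums to 0.1372 (unrounded). Noncentrality = 101 × 0.1372 = 13.86.
Power = Φ(√13.86 − 1.96) = Φ(1.763) = 0.961.
The N needed for exactly 0.96 is 100.3, so 101. With 42 patients the same test gives Φ(√5.76 − 1.96) = 0.67, so the printed figure needs all 101 patients.

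**3. What the stated rule delivers.** With 42 pN+ patients, 0.96 × 42 = 40.3, so the rule needs at least 41 true positives, that is, at most one false negative.

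- True sensitivity 0.99: 0.99⁴² + 42 × 0.01 × 0.99⁴¹ = 0.656 + 0.278 = 0.934.
- True sensitivity 0.96: 0.96⁴² + 42 × 0.04 × 0.96⁴¹ = 0.180 + 0.315 = 0.495.

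The number of pN+ patients is itself random. Averaged over Binomial(101, 0.42), the probabilities are 0.938 and 0.514. Reading the rule as more than 96% changes the first average only to 0.936.

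**4. Supporting check: would kappa values of 0.6 to 0.9 be plausible here?** This needs two assumptions. One is that kappa compares the mapping result with nodal status in the four cells that the Sample size section defines, where a pN0 patient with any fluorescence is a false positive. The other concerns f, the proportion of pN0 patients who fluoresce, which the document does not give. The sentinel-node detection rates cited in the Background, 91% (80–98%) and 94%, serve as a proxy.

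Observed agreement = 0.42 × 0.99 + 0.58 × (1 − f). Mapping-positive proportion q = 0.42 × 0.99 + 0.58f. Chance agreement = 0.42q + 0.58(1 − q).

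| f | Observed | Chance | Kappa |
|---|---|---|---|
| 0.80 | 0.532 | 0.439 | 0.17 |
| 0.91 | 0.468 | 0.429 | 0.07 |
| 0.94 | 0.451 | 0.426 | 0.04 |
| 0.98 | 0.427 | 0.423 | 0.01 |

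Kappa of 0.6 would need f of at most about 0.35, and kappa of 0.9 at most about 0.08.

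**The case against.** The strongest reply is that little changes. The sample size is right, both printed figures can be reproduced, and the chance of passing at a true sensitivity of 0.99 is only two to three points below 0.96. That stands: this is a correct number attached to the wrong analysis, and it calls for a reporting correction, not a redesign. It does not rescue the statement, because power also implies protection against passing a method that is not good enough, and the rule passes about half the time at its own threshold.

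Several stronger readings are tempting and are not supported.

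- *The kappa test could not succeed.* The document never says which two classifications kappa would compare. The detection rates come from sentinel-node studies, which the Background itself sets apart from whole-collector mapping. The assumption under Objectives that ICG fills the whole collector makes a low kappa plausible, but no more than that.
- *Kappa will never be computed.* The unnamed accuracy measures might include it, and a separate analysis plan may exist. What can be said is that this document names no kappa analysis.
- *The Design section relies on the 0.96.* It speaks of a "study protocol created to possibly minimize them and ensure that the statistical hypothesis is tested", but the risks meant there, type II error among them, are those of the single-centre approach, and it gives no power figure.
- *The trial has poor power in an exact test of sensitivity against a fixed value.* The plan states no such test. It compares the estimate with 0.99 ± 0.03 and applies a rule to the point estimate.

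**Conclusion.** The concern holds as a misstatement of one design property. The printed power of 0.96 matches a two-sided kappa test on all 101 patients (0.961). It does not describe the sensitivity endpoint, whose sample size is precision-based and carries no power. For the rule in use, the corresponding figures are about 0.94 at a true sensitivity of 0.99 and about 0.51 at 0.96. They assume 101 evaluable patients, 42% pN+ and independent patients.

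That the 0.96 came from this particular kappa test is inferred from the close match and from the adjacent kappa inputs. The conclusion that it is not a power for sensitivity does not depend on that inference. The low implied kappa (about 0.01 to 0.17 if 80–98% of pN0 patients fluoresce) is supporting evidence only, and the conclusion stands without it. Sample size, endpoint and planned analysis are not called into question by this point.

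**What to change.** In Sample size calculation and statistical analysis:

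1. Delete the sentence with the kappa values and the sentence with the power.
2. State that 101 is a precision-based size for sensitivity (0.99 ± 0.03, about 42 pN+ patients expected) and that no power is claimed.
3. Give both operating figures of the rule: with 101 patients and 42% pN+, an observed sensitivity of at least 0.96 has probability about 0.94 if the true sensitivity is 0.99, and about 0.51 if it is only 0.96. Giving the first alone would replace one reassuring number with another.
4. Use one form of the rule in the Abstract and the synopsis (at least 96%, or more than 96%); the numerical effect is negligible.

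The cost is a few sentences and a less favourable stated figure. No patients, data or analyses are added or changed.

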#### Endpoints

Primary endpoint
Proportion of pN+ patients in which affected lymph nodes are detected only within margins of ICG distribution (number of patients with affected lymph nodes located within ICG distribution margins divided by the number of all patients with pN+).

Secondary endpoints
Incidence of adverse events related to ICG lymphatic mapping (time frame: 30 days after operation);feasibility of ICG lymphatic mapping for colon cancer (proportion of cases with ICG spillage affecting interpretation);incidence of lymph node metastases outside conventional resection margins – 10 cm (proportion of patients with aberrant lymphatics leading to affected lymph nodes);colon cancer lymphatic spread pattern (descriptive data on incidence of D1, D2 and D3 lymphatic collector metastases and frequencies of D1 collector metastases depending on distance from primary tumor);proportion of operations which extent is effected by ICG lymphatic mapping (number of patients with change of operation plan due to mapping results divided by the number of patients).

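### The spread-pattern endpoint asks how often each lymph node collector is involved, but its stated analysis gives only a pooled ratio of affected to examined nodes

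*Protocol article*

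**What the plan says.** The Endpoints section of the protocol article defines the spread-pattern endpoint as "descriptive data on incidence of D1, D2 and D3 lymphatic collector metastases and frequencies of D1 collector metastases depending on distance from primary tumor".

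The section on sample size calculation and statistical analysis then fixes the statistic: "Lymph node metastases pattern will be assessed as calculation of frequency of affected nodes related to number of studied nodes in each group". Numerator and denominator are both counts of nodes. No patient-level proportion is given for this endpoint.

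Three other statements bear on how to read this:

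- A neighbouring secondary endpoint, the incidence of metastases beyond the 10 cm margins, is explained as "proportion of patients with aberrant lymphatics leading to affected lymph nodes". There, incidence is counted per patient.
- The Design section sets the unit of data collection: "During pathological examination each lymph node is assessed both for presence of metastases and for its exact location in relation to margins of ICG distribution". A single patient therefore contributes several nodes.
- The paragraph on secondary endpoints closes with a general sentence: "Parametric and non-parametric criteria will be used to compare mean values and contingency tables". It names no endpoint and no unit of analysis.

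**The concern.** The definition and the analysis answer different questions. The incidence of metastases in a collector is naturally the share of patients with disease there. It is also the form in which the result would inform resection extent, because that decision is made one patient at a time. The stated analysis gives the share of examined nodes that are positive.

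The node ratio also depends on how nodes are distributed over patients. A patient with a large harvest counts for more than one with a small harvest, and a few patients with many affected nodes can dominate the numerator. Harvest will vary: under Morphological assessment, nodes are marked according to the resection and lymphadenectomy performed, and under Patient enrollment the surgeon decides the extent of resection. Differences between D1, D2 and D3, or between distance bands, would then mix involvement with yield.

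A reader who takes the node ratio for the incidence named in the endpoint would conclude that a collector is involved several times less often than it is.

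**Working it through.** **The plan's own figure.** The only sample size in the document concerns the primary endpoint: "Sample size of 101 patients was calculated using Buderer method". It reproduces: 1.96² × 0.99 × 0.01 / 0.03² = 42.26 pN+ patients, and 42.26 / 0.42 = 100.6, rounded up to 101. The document gives no planning figure for the spread pattern, so there is none to check.

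**What the node ratio weights.** Let patient i have nᵢ examined and xᵢ affected nodes in a collector. The planned statistic is Σxᵢ / Σnᵢ, which equals the sum over patients of (nᵢ / Σn) × (xᵢ / nᵢ). Each patient's own fraction is weighted by yield. The patient-level incidence is the number of patients with xᵢ ≥ 1 divided by the number with nᵢ ≥ 1. If all patients contribute the same number of nodes, the first cannot exceed the second.

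**Size of the gap.** Inputs:

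- Prevalence of pN+: 0.42, from the protocol.
- q, the share of examined nodes affected in pN+ patients: assumed, 0.05 to 0.30.
- m, the examined nodes per collector: assumed, 5 to 20.

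Take every node in a pN+ patient to be affected independently with probability q. Then:

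- node ratio = 0.42 × q
- patient-level incidence = 0.42 × (1 − (1 − q)^m)

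At q = 0.10 and m = 10: 0.42 × 0.10 = 4.2%, against 0.42 × (1 − 0.9¹⁰) = 0.42 × 0.651 = 27.4%. At q = 0.20 and m = 10: 8.4%, against 0.42 × (1 − 0.8¹⁰) = 0.42 × 0.893 = 37.5%.

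| q | Node ratio | Incidence, m = 5 | m = 10 | m = 20 |
|---|---|---|---|---|
| 0.05 | 2.1% | 9.5% | 16.9% | 26.9% |
| 0.10 | 4.2% | 17.2% | 27.4% | 36.9% |
| 0.20 | 8.4% | 28.2% | 37.5% | 41.5% |
| 0.30 | 12.6% | 34.9% | 40.8% | 42.0% |

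Over this grid, incidence exceeds the node ratio by a factor of 2.8 (34.9 / 12.6) to 12.8 (26.9 / 2.1).

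**Sensitivity to the independence assumption.** Suppose instead that the collector is involved in only half of pN+ patients, with twice the node probability there. At q = 0.10 and m = 10 the node ratio is still 4.2%, and the incidence is 0.42 × 0.5 × (1 − 0.8¹⁰) = 0.21 × 0.893 = 18.7%. The gap shrinks but remains more than fourfold.

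**Clustering, if node-level inference were done.** About 58% of patients are pN0 and contribute only negative nodes. This alone gives a within-patient correlation of 0.58q / (1 − 0.42q), which is 0.03 at q = 0.05 and 0.20 at q = 0.30. With an assumed 6 nodes per group, the design effect 1 + (m − 1) × ICC is 1.15 to 2.00, so standard errors are too small by a factor of 1.07 to 1.41.

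The size of a naive chi-square test at nominal 0.05 was simulated with 101 patients, 12 to 30 nodes per patient and q from 0.1 to 0.3:

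- patient subgroups compared: 0.14 to 0.46
- node groups within patients, involvement specific to each group: 0.11 to 0.41
- node groups within patients sharing one patient effect: about 0.03 to 0.045

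**The case against.** The strongest reply is that the endpoint is called descriptive and that the statistical section states openly that it divides nodes by nodes. A node-positivity ratio is a legitimate description. It is a different quantity from patient incidence, not a biased estimate of it. That is correct, but the endpoint promises the incidence, and the stated analysis does not produce it.

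A second reply is that D1 frequencies by distance can be read as node frequencies, which the plan delivers. This also stands, so the mismatch is clear only for the D1/D2/D3 incidence. Incidence is not expressly defined per patient for this endpoint; that reading rests on usual meaning and on the neighbouring endpoint.

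A reader might infer more: that node-level contingency tests are planned here, and that intervals and p-values will be too narrow. The document does not support this. The sentence on parametric and non-parametric criteria is general, and no interval or test is stated for the spread pattern. The spread pattern is missing from the list that begins "Descriptive statistics will be used to depict feasibility of ICG lymphatic mapping, incidence of adverse events, incidence of lymph node metastases outside conventional resection margins", so a test is possible, but it is not stated. A descriptive ratio assumes no independence, and the simulation shows that the direction of any error depends on the comparison.

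Nor does the node ratio necessarily fall as harvest grows. It does so only if the added nodes are less often affected than those already counted.

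**Conclusion.** The point holds as a mismatch between a defined secondary endpoint and its stated analysis. Followed as written, the plan reports how many examined nodes are positive, not how often a collector is involved. At 42% pN+ and the assumed node counts, the two differ by a factor of about 3 to 13. The exact factor rests on assumed yields and node positivity, which the document does not give; a several-fold gap also remains under the less favourable involvement pattern tried.

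The clustering point is conditional: it applies only if node-level intervals or comparisons are made, and the error could then be liberal or slightly conservative.

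The consequence is limited to this secondary endpoint. The primary endpoint and the endpoint on metastases beyond 10 cm are already counted per patient, and N = 101 is unaffected.

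**What to change.** In the section on sample size calculation and statistical analysis, make the main spread-pattern analysis a patient-level proportion for each collector (D1, D2, D3) and each D1 distance band. The numerator is patients with at least one affected node in that group or band. The denominator is patients in whom it was harvested and examined. Give an exact confidence interval, and show the denominator each time, since it will vary with the extent of resection.

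Keep affected over examined nodes as a supplementary description, labelled as a node ratio. Add that any node-level interval or comparison will use a method clustered by patient, such as GEE, a mixed model or a cluster bootstrap.

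The cost is a change of wording. Status and location are already assessed for every node, so no further data, patients or procedures are needed.

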This situation can be explained by the fact that presence of fluorescence is affected by tumor factors. Kakizoe *et al* compared distribution of cancer sites in lymphatic nodes according to hematoxylin and eosin staining to fluorescent picture: lymph nodes occupied by cancer cells up to 90–100% showed no fluorescence, and in nodes with smaller proportion of occupation fluorescence was missing in cancer sites^[8]^. The same pattern was observed by Ushijima *et al*, who also reported negative correlation between such factors as tumor’s depth of invasion and presence of fluorescence, and pN+ and presence of fluorescence respectively^[9]^. So, in cases of colon cancer focusing on fluorescence of specific lymphatic nodes, or seeking for sentinel nodes with ICG lymphangiography does not seem to be a reliable approach.

On the contrary, ICG imaging of the whole locoregional lymphatic collector is beneficial. Repeatedly reported data on surgical results after ICG mapping suggest that lymph node mapping without focusing on specific nodes might be useful for identifying resections’ extent during operations for colon cancer. In a series of 18 patients, Cahill *et al* observed 22% of fluorescing lymphatic nodes outside the initial resection plan^[10]^. Nishigori *et al* reported ICG lymph node mapping led to 23.5% change in the extent of lymphadenectomy, and 16.7% change in the colon resection plan^[11]^. Moreover, Watanabe *et al* reported that in cases of central vascular ligation, the use of ICG helped to identify appropriate central vessels to be dissected, as well as to determine the appropriate separation line of mesentery so that the whole observed lymph flow is included into specimen^[12,13]^. And Daibo *et al* showed that indocyanine green fluorescence imaging-guided laparoscopic right-sided colectomy could increase the number of total, intermediate, and central lymph nodes retrieved^[14]^. Thus, it seems that multiple groups of patients are likely to benefit from ICG lymphatic mapping, because this technique provides a possibility to tailor resection margins so that they fulfill oncological demand of regional lymphatic flow removal. Trial registration information is presented in Table 1.

**Table 1 T1:** Trial registration

Primary registry and trial identifying number	ClinicalTrials.gov NCT05468827
Date of registration in primary registry	21.07.2022

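### The general missing-data rule has no exemption for the primary endpoint, so as written it can delete that endpoint or impute it from almost no events

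*Protocol article*

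**What the plan says.** Under Endpoints, the primary endpoint is a proportion: "number of patients with affected lymph nodes located within ICG distribution margins divided by the number of all patients with pN"+ status. The section Sample size calculation and statistical analysis estimates it as sensitivity, the "number of true positive cases divided by sum of true positive and false negative cases". A pN+ patient with metastatic nodes outside the fluorescent zone is a false negative. Table 2 regards the method as potentially reliable if observed sensitivity is 96% or higher.

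The same statistical section gives the rule for missing data. On one side of the limit, "should more than 10% of data be missing, the variable will be deleted, because estimates are likely to be biased". On the other, "In other situations multiple imputations will be used". The rule covers all variables alike. It makes no exception for the primary endpoint, and it does not say whether the 10% is taken over all patients or over pN+ patients.

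That section also requires an intent-to-treat analysis of everyone enrolled, whatever treatment they received. Patients with unsuccessful ICG injection are set aside only in the per-protocol analysis. Under Endpoints, spillage that affects interpretation is expected often enough to be the measure of feasibility.

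**The concern.** The primary endpoint needs the metastatic nodes of each pN+ patient placed inside or outside the ICG margin. After spillage or a failed injection that may be impossible even though pN status is known. Under intent-to-treat such a patient stays in the analysis, and the general missing-data rule is the only handling the article states.

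Both branches of the rule suit this endpoint badly. Above 10%, the variable the trial exists to estimate is dropped. The stated reason is likely bias, but deleting a variable does not cure bias; it only leaves no estimate. At or below 10%, inside/outside status is imputed by a model that has almost no false negatives to learn from, so the filled-in values largely reflect the model's assumptions.

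The result is meant to inform whether resection can be reduced to fit the ICG spread (Objectives and study hypothesis). An estimate that depends on how a few unreadable maps are filled in is a weak basis for that.

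**Working it through.** **Inputs from the protocol article.** "estimated sensitivity of 0.99 and precision (margin of error) of 0.03"; confidence level 0.95, taken as two-sided (z = 1.96); pN+ prevalence 42%; N = 101; success at 96% or higher; missing-data limit 10%.

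**1. The plan's own sample size.**
- pN+ needed = 1.96² × 0.99 × 0.01 / 0.03² = 42.26.
- Total = 42.26 / 0.42 = 100.6, rounded up to 101. The stated figure reproduces.
- Expected pN+ patients = 101 × 0.42 = 42.4, so 42 is used below.

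**2. Where the deletion branch starts.**
- Base of 101 patients: 10/101 = 9.9% (imputed); 11/101 = 10.9% (deleted).
- Base of 42 pN+ patients: 4/42 = 9.5% (imputed); 5/42 = 11.9% (deleted).

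**3. Events available to an imputation model.** Expected false negatives = 42 × (1 − sensitivity).
- At 0.99: 0.42, with P(none) = 0.99^42 = 0.66.
- At 0.96: 1.68, with P(none) = 0.96^42 = 0.18.

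The model therefore has about 0 to 2 events.

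**4. Room in the success rule.** 41/42 = 97.6% passes and 40/42 = 95.2% fails, so one false negative is tolerated. If none is observed and two pN+ patients are uninterpretable, the result is 42/42 or 40/42, depending only on how those two are counted.

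**5. Illustrations (assumed counts).**
- 3 of 42 uninterpretable, no false negative observed: about 100% if imputed as true positives; 39/42 = 92.9% if counted as failures.
- 4 of 42 uninterpretable (9.5%, so imputed), no false negative observed: the possible range is 38/42 = 90.5% to 100%. A simple beta-binomial imputation gives a mean of 99.9% (Jeffreys prior) or 99.8% (uniform prior).
- 4 of 42 uninterpretable, one false negative observed: the possible range is 37/42 = 88.1% to 41/42 = 97.6%. The mean after imputation is 97.3% (Jeffreys) or 97.1% (uniform), and 14% or 18% of imputed data sets hold two or more false negatives and so miss 96%.

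**6. Chance of crossing 10% of 101 patients.** The documents give no missingness rate, so the rate q is an assumption. P(X ≥ 11), X ~ Binomial(101, q):

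| Assumed q | P(variable deleted) |
|---|---|
| 2% | below 0.001% |
| 5% | 1% |
| 6% | 4% |
| 9% | 30% |
| 10% | 43% |

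**The case against.** The strongest reply is that the rule is loosely worded boilerplate, that missing margins may be rare, and that much of the remedy already exists. Surgery is recorded, marked specimens are photographed, and all data are verified. Spillage is reported as its own endpoint, and the per-protocol analysis already sets aside unsuccessful injections. All of this is true, and it lowers the likely damage. It does not change the intent-to-treat analysis, where the rule applies as written.

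A reader might also infer four stronger things that the documents do not support.

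- **That the protocol itself predicts 6–9% missing margins.** The background section cites detection rates of 94% and 91% (80–98%), but these are for sentinel-node procedures, which the article expressly separates from mapping the whole lymphatic collector. They are not a missingness rate for ICG margins.
- **That a pN+ patient with no fluorescence is missing data.** On the article's definitions such a patient is most naturally an observed false negative, with nothing to impute. Nor is an unoperated patient a missing pN+ case, because without a specimen there is no pN status.
- **That missingness is shown to be informative.** The background reports negative correlations of fluorescence with depth of invasion and with pN+. That concerns whether fluorescence is present, and says nothing about spillage or failed injection.
- **That imputation always pushes sensitivity to 1.** It comes close when no false negative is observed. With one observed, some imputed data sets fall below 96%.

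**Conclusion.** The concern holds for a rule the article states, so it is not a matter of detail left to a fuller document. Applied literally, the rule discards the primary variable at 11 of 101 (or 5 of 42 pN+) missing. Below that it fills in inside/outside status from about 0.4 to 1.7 expected false negatives, when the success rule has room for only one. The verdict can then turn on two uninterpretable pN+ patients, or on one if a false negative has already been observed.

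This rests on about 42 pN+ patients, on spillage and failed injection being the source of unreadable margins, and on reading the rule as covering the primary endpoint because nothing exempts it. How often it would matter cannot be derived from the document: the chance of deletion runs from negligible at 2% missing to 43% at 10%. The rule should be corrected before results are known. With no documented missingness rate, calling it a fault that must defeat the primary analysis would go too far.

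**What to change.** Replace the missing-data paragraph for the primary endpoint as follows.

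- Exempt the endpoint and its components (ICG margin status, node location relative to it) from both deletion and imputation.
- State that a pN+ patient with no fluorescence after a technically adequate injection counts as a false negative.
- Report sensitivity among pN+ patients with an interpretable ICG margin. Beside it, give two bounds: all uninterpretable pN+ patients counted as true positives, then all counted as false negatives.
- Limit multiple imputation to descriptive covariates, if it is used at all.

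The cost is one paragraph, two extra table rows and a wider reported range. In a case such as 39 of 39 interpretable patients inside the margin, the main estimate would still be 100%, but the reader would see the 92.9% lower bound beside it.
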